### Development of the intervention

The T4TM intervention was developed based on the Healthy Babies through Infant-Centered Feeding intervention curriculum [64], which provided evidence that education about infant-centered feeding had a positive impact on low-income mothers’ infant feeding knowledge and self-reported feeding behaviors. Behaviors targeted in the T4TM intervention were derived from theories and empirical studies of mother-infant interaction [86,89-91]. The infant-centered feeding experience comprises maternal responsiveness (MR), feeding styles (FS), and feeding practices (FP). Maternal responsiveness is maternal behavioral sensitivity to infant cues through accurate recognition and judgment of what the infant needs [91-97]. Feeding style pertains to the mother’s beliefs about and approach (authoritative, authoritarian, permissive, or uninvolved) to guiding her infant’s feeding behaviors [97-101]. Feeding practices are maternal behaviors relating to what, where, how, and how often a baby is fed [99]. Maternal behaviors affect infant growth over time [102-119].

Previous research by the Principal Investigators to inform the development of T4TM challenge content, activities, and design included focus groups in which adolescent mothers identified areas of interest and need related to infant-centered feeding practices [120]. Results from two focus groups with low-income, adolescent, first-time mothers of infants [121] (N = 16) revealed interests in: a) lessons on infant feeding, b) learning about the proper introduction of solid food, c) how much formula babies should be receiving, and d) learning to recognize hunger and satiation cues.

### Participants and recruitment

To be eligible, a potential participant must: be low-income (≤185% federal poverty level in the United States and eligible for MIHP services), be between 15 and 19 years of age at time of enrollment, be a first time mom, have an infant two months of age or less, be a primary caregiver who feeds her infant at least once a day, have text messaging and web access, and have had a term birth (37 ≤ 42 weeks, 2500 ≤ 3750 grams birth weight). If either mother or infant has been diagnosed with an eating or nutritional condition, the dyad is ineligible. Staff members from MIHP offices in four Michigan counties target mother-infant dyads, providing information about the study to recruit mothers with infants or expectant mothers to enroll in the project.

Once eligibility is established, families are contacted for the initial data collection home visit where written informed consent is obtained. We have institutional approval to conduct this trial from the University Committee on Research Involving Human Subjects from Michigan State University.

### Randomization

Data collection packets are pre-randomized into either T4TM or control group, keeping the assigned group blind to the data collectors until they arrive at participants’ homes to conduct the baseline data collection. Participants are randomly assigned via computer randomization procedure using Microsoft Excel, balancing groups by the four county recruitment sites.

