### Procedures

Data are obtained by trained data collectors using both self-report questionnaires and anthropometric assessment. To ensure consistency and accuracy of data collection, a half-day intensive training session was held for data collectors prior to the collection of data, to be followed by a booster session in year 2. Training consisted of a standardized training guide and protocol including review of the instruments and measurement of infant recumbent length and weight. Telephone contact and email communication occurs between the project manager and the data collector and/or supervisor to facilitate open communication and fidelity to the protocol.

Intervals for data collection reflect time points (at infant age of 4–8 weeks, 3 months, and 6 months old) that align with both infant feeding recommended milestones and the intervention duration. For example, the third data collection occurs when the infant is 6 months old, when solids foods introduction is recommended.

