#### Infant outcome

**Infant growth** is the measurement of an infant’s weight and length plotted over time using *z* scores computed from the measures taken at T1 (baseline),T2, post intervention; and T3. Infant weights and lengths will be standardized as weight-for-age percentiles (WAP) and weight-for-age *z*-scores (WAZ), using WHO Anthro [140]. Relative weight gain (or loss) can then be calculated as the difference between WAZ scores at T3 and T1 [140]. Rate of growth proportional to birth weight and body composition (a weight-for-length index) will also be calculated. We expect a greater proportion of infants in the intervention group: 1a) will fall below the 85th percentile of the WHO growth norms at three and six months; and 1b) z score change <0.67 in weight-for-age WHO norms over time periods one-to-three months, and three-to-six months.

The infant’s weight and length is measured at all three time points to provide an objective measure of weight status. The infant is weighed in a clean diaper on an electronic scale and weighed to the nearest half ounce. Infant length is measured in the recumbent position. Digital scales are calibrated prior to weights being taken. These data will be entered into EpiInfo V3.4.3 to calculate weight-for-length z scores.

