### Data analysis

Outcomes (infant growth, MR, FS, FP) and maternal and infant factors at baseline (self-efficacy, knowledge, infant age, temperament, type of feeding) will be compared across intervention and control groups using t-test for continuous variables and chi-square test for categorical variables [149,150]. If differences are observed, the relevant variables will be treated as covariates in our post-experiment analyses [149,151,152]. All analyses will use the intention-to-treat [153] principle based on imputed data. The hypothesis regarding differences in outcomes at each follow-up T2 and T3 between intervention and control groups will be tested using the generalized estimating equation (GEE) model [154] for proportional group differences in growth over time. To explore efficacy of the intervention as assessed by MR, FS, FP, evaluated pre-intervention (T1), immediately post intervention (T2), and when the infant is six months old (T3). Both general linear mixed models (GLMM) [155,156], for continuous outcomes and the GEE model for logistic or Poisson regression for binary/ordinal and count outcomes will be considered.

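### As worded, the data collectors' blind ends on arrival at the home, so the arm can be known before consent is signed and before baseline is recorded

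*Protocol article*

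**What the plan says.** The protocol article fixes the relevant steps in three places.

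- **Randomization.** The arm is attached to the packet in advance, and the end of the blind is stated: "Data collection packets are pre-randomized into either T4TM or control group, keeping the assigned group blind to the data collectors until they arrive". The arrival meant is at the home, for the baseline visit. Assignment is generated in a spreadsheet and balanced over the four counties.
- **Participants and recruitment.** Eligibility comes before the visit: "Once eligibility is established, families are contacted for the initial data collection home visit". Consent is taken at the visit: "families are contacted for the initial data collection home visit where written informed consent is obtained".
- **Procedures.** The collectors take all measurements: "Data are obtained by trained data collectors using both self-report questionnaires and anthropometric assessment".

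Two further sentences show where baseline values go. Infant outcome: "Relative weight gain (or loss) can then be calculated as the difference between WAZ scores at T3 and T1". Data analysis: "If differences are observed, the relevant variables will be treated as covariates in our post-experiment analyses".

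The article nowhere says that the packet, or the assignment inside it, stays closed until consent is signed or baseline is complete.

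**The concern.** Allocation has to stay hidden until the participant is enrolled. A blind that ends on arrival protects scheduling and travel, but not the consent conversation or the baseline measurements that follow.

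Two things are at stake.

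- **Selection.** A collector who knows the arm may present the study differently, or the mother may decline once the arm becomes apparent. The control arm adds nothing to the programme care that these mothers already receive, so consent that differs by arm is plausible. A mother who declines before signing never becomes a participant. Intention-to-treat analysis on imputed data then has no record of her to work with.
- **Baseline measurement.** Maternal responsiveness, feeding style and feeding practices are reported by questionnaire at a visit run by someone who may know the arm. Recumbent length depends on the operator.

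The article describes the trial partly as preparation for a larger study, with estimation of the effect size first among its foci. A biased estimate would carry over into that study's planning.

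**Working it through.** **1. Order of events, from the sections set side by side**

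| Step | Where stated | Collector's knowledge of the arm |
|---|---|---|
| Packet assigned to an arm | Randomization | hidden |
| Eligibility established | Participants and recruitment | hidden |
| Collector arrives at the home | Randomization | blind ends |
| Written consent | Participants and recruitment (same visit) | may be known |
| T1 questionnaires, weight, length | Procedures; Infant outcome | may be known |

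The order of the last two rows relative to opening the packet is inferred from the stated end of the blind. No sentence gives a different order. That the collector is the person who takes consent is also an inference: the article places no other staff at this visit.

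**2. Where T1 values are used**

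- They enter the T3 minus T1 difference in weight-for-age z-score, the one-to-three-month change in H1b, the T1 to T3 models for the maternal outcomes, and the choice of covariates.
- They are not part of H1a (below the 85th percentile at three and six months), the three-to-six-month change in H1b, or H2c (age at introduction of solids).
- Weight-for-age uses weight, which is read from a calibrated electronic scale. Length enters only the weight-for-length measures. The T1 values most open to influence are therefore the maternal scales and length.

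Selective consent is different: it changes who is in each arm, so it can reach every outcome.

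**3. Illustration of size**

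Inputs from Sample size and power calculations: 40 per group, one-tailed 0.05, power 0.80, m = 3 measures, compound symmetry with the stated 0.20 read as the correlation. No effect size is given, so the 40 per group cannot be reproduced; it can only be solved backwards.

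- Formula: n per group = 2(z_α + z_β)²[1 + (m − 1)ρ] / (m d²).
- Solved for d: √[2 × (1.645 + 0.842)² × 1.4 / (3 × 40)] ≈ 0.38 SD.

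Shift from selective loss: removing a fraction f of one arm, whose mean differs by δ from the rest, moves that arm's mean by f × δ. Both f and δ are assumed.

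- f = 0.10, δ = 0.5: 0.05 SD, and 0.05 / 0.38 = 13%.
- f = 0.10, δ = 1.0: 0.10 SD, and 0.10 / 0.38 = 26%.

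Effect on the one-sided test, if the shift favours the intervention and persists over the three measures:

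- Standard error of the time-averaged contrast: √(1.4 / 3) × √(2 / 40) = 0.683 × 0.224 ≈ 0.153 SD.
- Type I error: 1 − Φ(1.645 − shift / 0.153).

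| Assumed shift (SD) | One-sided type I error |
|---|---|
| 0 | 5% |
| 0.05 | about 9% |
| 0.10 | about 16% |
| 0.20 | about 37% |

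A shift in the other direction would hide a true effect instead.

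**The case against.** The best case for the plan has four parts.

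- **Concealment is partly in place.** Programme office staff approach the mothers, eligibility is settled before the visit, and the collectors are blind up to the door. This stands. A reader might infer that allocation is open throughout, or that an unblinded person decides eligibility; the article says the opposite. The exposed stretch runs from arrival to the end of baseline.
- **The order within the visit is not spelled out.** Procedures refers to a training guide and protocol that are not shown, and an article may leave visit details to such a document. This stands as a limit on certainty. But the article is not silent: it states when the blind ends, and that moment comes before consent. If practice already keeps packets closed for longer, the sentence is wrong and still needs changing.
- **The primary infant outcome is weight, measured objectively.** This stands for measurement: weight is hard to shade, and nothing says that the mother is told her arm before she completes the questionnaires. It does not answer selective consent.
- **This is largely a feasibility study.** That lowers the stakes, but H1 and H2 are still tested and the effect size is meant to inform a larger trial.

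Two further readings are tempting. One is that T1 is the reference for every outcome, so that all results inherit a distorted baseline. The hypotheses do not support this, as the list of T1 uses shows. The other is that the same unblinded collectors return at T2 and T3. The article does not say who attends those visits.

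**Conclusion.** The point holds in this form: the stated end of the collectors' blind comes too early, so allocation is not concealed through consent and enrolment, and baseline is not protected from knowledge of the arm. This rests on reading two sections together and on taking the stated end of the blind at its word.

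The size is unknown. The 0.05 to 0.10 SD shift, and the rise in type I error to about 9% to 16%, depend on an assumed 10% selective loss and an assumed difference of 0.5 to 1.0 SD. The ratio of 13% to 26% also depends on a back-solved 0.38 SD. That figure is a continuous time-averaged difference, whereas H1 compares proportions, so a reader should not take the ratio as the bias in the primary comparison. The defect does not depend on these figures.

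Analysis cannot restore mothers who declined before signing, so the protection has to come from the procedure.

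**What to change.** Change the Randomization section to say that the assignment lies in a sealed, opaque, sequentially numbered inner envelope within each county's series. The envelope is opened only after consent is signed and all T1 questionnaires and anthropometry are recorded.

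The cost is re-packing the data collection packets and adding one line to the collectors' guide. No extra staff, visits or participants are needed. If the packets are already handled in this way, only the sentence in the article has to change.

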### Sample size and power calculations

Using non-intervention levels of infant growth to determine sample size, a power analysis using a time-averaged difference (TAD) method [147] indicated a sample size of 80 participants (40 per group) would be necessary to achieve power at .80, with a one-tailed TAD p < 0.05 over three measures and assuming a compound symmetry covariance structure with p = 0.20. A sample of 80 is deemed adequate; it is higher than the often recommended 12 per group [148]. The primary foci of this study include assessment of: 1) the effect size of the intervention to power a larger study, 2) feasibility, 3) practicality of data collection procedures, 4) measurement adequacy, and 5) the ability to implement.

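### Allocation is balanced on county, but the covariate rule would not be expected to bring county into the models; if county is prognostic, the analysis of continuous outcomes is mildly conservative

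*Protocol article*

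**What the plan says.** The Randomization section of the protocol article describes a computer-generated allocation, "balancing groups by the four county recruitment sites". It names no other balancing factor and gives neither a block size nor an algorithm.

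The Data analysis section compares the arms at baseline on the outcomes and on "maternal and infant factors at baseline (self-efficacy, knowledge, infant age, temperament, type of feeding". County is not in that list. The rule that follows is: "If differences are observed, the relevant variables will be treated as covariates in our post-experiment analyses".

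On the models, the infant-growth hypothesis "will be tested using the generalized estimating equation (GEE) model", and for the maternal outcomes the section names "Both general linear mixed models (GLMM) [155,156], for continuous outcomes and the GEE model for logistic or Poisson regression". No county or site term is mentioned for any of them. The sample size section does not mention county either.

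**The concern.** The two sections pull in different directions. Balancing on county keeps most between-county variation out of the difference between arms. A model without county still counts that variation as error. When county is related to the outcome, the reported standard error then exceeds the true one, the confidence interval is too wide, and the test rejects less often than its nominal level under the null.

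The article does more than leave the covariates open. It ties adjustment to observed baseline differences, and a factor balanced by design is the one least likely to meet that criterion. Listing county among the compared factors would therefore change little.

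A county effect is plausible, because recruitment and usual care both run through county-based MIHP offices and usual care follows individual plans. That is an inference; the article reports no outcome data by county.

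Precision is at stake. The sample size section makes estimation of the effect size for a larger study one of the trial's main purposes, and the retention goal is only 40 per group.

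**Working it through.** **The plan's own figure.** The sample size section gives "a sample size of 80 participants (40 per group") that "would be necessary to achieve power at .80", "with a one-tailed TAD p < 0.05 over three measures", with compound symmetry and a correlation of 0.20 (printed as p, read here as rho). No effect size is stated, so 80 cannot be reproduced, only solved backwards. With m = 3 measures, the variance of a dyad's mean, in units of the single-measure variance, is

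D = [1 + (m − 1)·rho]/m = (1 + 2 × 0.20)/3 = 0.467.

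The detectable standardised difference with 40 per arm is

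d = sqrt[2 × (1.645 + 0.842)² × 0.467/40] = 0.38.

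This value is used below only to express the loss as power.

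**Effect of leaving county out.** Let s be the share of the variance of the analysed continuous outcome that county explains. It is not in the documents, so a range is assumed. With arms balanced within county and a linear model:

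- reported SE / true SE = 1/sqrt(1 − s)
- true one-sided level = 1 − Phi[1.645/sqrt(1 − s)]

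| s (assumed) | SE ratio | SE overstated by | 1.645 × ratio | True one-sided level |
|---|---|---|---|---|
| 0% | 1.000 | 0% | 1.645 | 0.050 |
| 2% | 1.010 | 1.0% | 1.662 | 0.048 |
| 5% | 1.026 | 2.6% | 1.688 | 0.046 |
| 10% | 1.054 | 5.4% | 1.734 | 0.041 |

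**The definition of the share matters.** If the percentage refers to a single measurement and the county effect is constant over time, averaging three measures shrinks the other variation but not the county effect, so s = share/0.467. Power without county is Phi[(d/SE_rep − 1.645)/sqrt(1 − s)] and with county Phi[(d/SE_rep)/sqrt(1 − s) − 1.645], where d/SE_rep = 0.380/sqrt(2 × 0.467/40) = 2.486.

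| Share of single-measure variance (assumed) | s for the mean of three | SE overstated by | One-sided level | Power without county | Power with county |
|---|---|---|---|---|---|
| 1% | 2.1% | 1.1% | 0.048 | 80.3% | 80.8% |
| 2% | 4.3% | 2.2% | 0.046 | 80.5% | 81.5% |
| 5% | 10.7% | 5.8% | 0.041 | 81.4% | 83.8% |
| 10% | 21.4% | 12.8% | 0.032 | 82.9% | 87.7% |

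**Check by simulation.** The set-up was 20,000 trials per scenario, a continuous outcome, four counties of 20 dyads and permuted blocks of 4 (county sizes and block size are assumptions). For single-measure shares of 0, 2, 5 and 10%, the one-sided type I error was 0.049, 0.045, 0.041 and 0.032 without county, and 0.049, 0.049, 0.050 and 0.050 with it. This agrees with the formula in direction and size. The binary outcomes were not simulated.

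**The case against.** **The article is condensed.** It writes out no model, says only that the mixed and GEE models will be considered, and nowhere excludes county. A reader might infer that the plan adjusts only for variables that differ at baseline. The word "only" is not in the text, and a full protocol or SAP could add county. That stands as a limit on the wording. It does not remove the point, because the one adjustment criterion the article publishes is observed difference, and that criterion points away from county.

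**County could still enter.** A reader might infer that county can never become a covariate. The documents do not support that. The balancing method is not given, so exact balance is not established, and losses between the 100 anticipated and the 40 per group retained could unbalance the counties among those measured. Intention-to-treat analysis on imputed data limits this.

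**County may not be prognostic.** Both arms in all four counties receive the same MIHP programme, eligibility narrows the sample on income, age, parity, gestation and birth weight, and infant weight is standardised to WHO norms. If county has no effect, the level is correct and no precision is lost. This stands in full.

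**The formula does not fit the primary hypothesis directly.** H1 concerns proportions. In a logistic model, adding a prognostic covariate does not generally shrink the standard error of the coefficient; it changes the odds ratio from marginal to conditional. H1b rests on a change in z-score, from which stable county differences largely cancel, as they do from a group-by-time contrast. This stands too, so the figures above apply only to comparisons of level on continuous outcomes.

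**County terms can be sparse.** Suppose 15% of infants exceed the 85th percentile (taken from the definition of the norm) and counties hold 20 each (assumed). Then 80 infants give about 12 events, and the chance that at least one county has none is 1 − (1 − 0.85^20)^4 = 1 − (1 − 0.039)^4 = about 15%. Logistic county terms could then fail to be estimable. This is a reason to treat the binary outcomes differently.

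**Conclusion.** The point holds as a minor but worthwhile correction. The design balances on county, and the published covariate rule would not be expected to carry county into the analysis. If county explains 2% to 10% of the variance of a continuous analysed outcome, standard errors are about 1% to 5% too large and the one-sided level falls from 0.05 to about 0.048 to 0.041. If the share is read as that of a single measurement, the effect on a three-measure mean is larger: at shares of 1% to 5%, including county gains about 0.5 to 2.5 points of power.

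The size rests on an assumed county share, on arms balanced within county, and on a linear model for a continuous outcome. For the binary outcomes no size is claimed.

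A reader might infer that the trial's test is invalid or its effect estimate distorted. Neither follows. The treatment effect is not biased, false positives are not inflated, and without a county effect nothing is lost.

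**What to change.** - **Continuous outcomes:** state that county enters every mixed model as a prespecified fixed covariate (three indicator terms), whatever the baseline comparisons show.
- **Binary H1 outcomes:** report a county-stratified (Mantel-Haenszel) or county-standardised risk difference. Fix before unblinding the rule for merging a county with too few infants or events.
- **Covariate rule:** add that selection by observed baseline differences does not apply to the factor used in allocation.

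The cost is three degrees of freedom out of about 80, a few sentences of analysis text, and the possibility of sparse county cells in the binary analyses, which the merging rule is there to handle. Sample size, data collection and conduct do not change.
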